#### During laboratory visits for each data point

All participants will have the chance to use the toilet upon arrival at the laboratory. All participants will also be offered a half cup of water in order to attempt to equalise current levels of water intake in combination with the pre-attendance requirements (i.e. those who are less sated will be more likely to take up the offer). The pre-task procedures will be checked; participants will be rescheduled if necessary (such as if caffeine had been consumed). Mobile phones will be switched off prior to the start of experimentation.

Participants will undertake the spatial cueing task followed by the stop/signal task, then by a measure of interoception involving heart beat estimation, all on a laptop computer. This will be followed by further tests of interoception, including a water load test and a self-report tool. All tasks will take place in a physiology laboratory (with light attenuation on the first two tasks).

Heart activity will be measured using ECG throughout all computer tasks. This is commonly found in emotion studies as an objective indicator of affective changes. Heart rate variability (HRV) is measured by beat-to-beat changes in heart rate [51], where greater HRV is an indication of adaptability and has been associated with inhibitory processing (e.g. [52–54]). Rapid heart rate deceleration has been established to occur following the presentation of external stimuli [55, 56], but which is more marked when viewing emotionally negative stimuli (see [57, 58]). By taking continuous ECG measurements, this deceleration can be recorded and linked to the presentation of individual stimuli. In order to link the ECG with the stimulus presentation software, an audible tone will be the first event in each task, played through headphones with a microphone inserted into a speaker. The microphone will be plugged into the acquisition and analysis system *PowerLab* 16SP (*ADinstruments*). *SuperLab* will be set up to track the cumulative time (in milliseconds) throughout trials, so that the initial tone will then be the reference point for all other measurements in both *SuperLab* and *PowerLab* (using *Labchart* software, *ADinstruments*). Because the sound is played through headphones before each participant begins, this will have no relevance to any other tone played during the stop/signal or the Schandry task (the spatial cueing task involves no tones in its procedures). The magnitude of the heart rate deceleration (and “heart rate variability” more generally) can then be used as an objective physiological indicator of emotional responses.

In addition, constant measurement of heart rate will permit control of the influence of the systole heartbeat phase on responses to threat/fear stimuli (i.e. compared with diastole, responses to such stimuli during systole lead to greater arousal and are likely to be quicker [59]). This has the potential to create unmeasured variability in the data if stimuli are presented at varying heart phases.

Participants may attend with loose-fitting clothing, or a scrubs top will be supplied; this is to allow easy application of the ECG electrodes (which will be self-applied according to given instructions). A 3-lead ECG will be recorded with surface Ag/AgCl electrodes on the chest in standard configuration (*ADinstruments* ECG, NZ). *PowerLab* will be set at a sampling rate of 1 k/s, and with a range of 100 mv.

Participants will move to a seated position in an enclosed booth to prevent visual distractions. They next rest their head in a chin rest to prevent overt orienting, facing a computer screen (*Apple Macbook Pro* 15-inch laptop screen) at a horizontal distance of 45 cm from eye position and access a mouse to the right-hand side. To ensure the comfort of each participant, an adjustable height desk will be used.

In order to be able to answer any questions and, insofar as possible, to monitor adherence to the task instructions, the researcher will be seated at the far side of the laboratory room throughout the tasks, but unable to see/observe the participant.

#### Spatial cueing task

This will address RQ1 and RQ2. To address RQ1, an emotional cross-modal^1^ spatial cueing task will be used to record RTs to emotional stimuli (the *International Affective Picture System*, or IAPS; the *Nencki Affective Picture System*, or NAPS) when detecting activity at a location. The IAPS [60] is a well-established set of emotional stimuli, reliably inducing affect with short presentation duration [61], and without habituation during repeated exposure to same-valence images [62, 63]. The NAPS is a more recently developed, less widely used, but still validated visual stimulus set [64] using the *Self-Assessment Manikin* (SAM), which was also used for standardising ratings of arousal and valence in the IAPS.

The IAPS stimuli have been shown to elicit physiological responses, with one study [65] finding heart rate variability responses with images rated at arousal levels of ≥ 4.5 (based on the scale for SAM, 1–5, where in this case 5 was the highest level of arousal). If erotic imagery is excluded, negative emotional images that produce defensive responses, such as pictures of human or animal attack, tend to be the most highly arousing [66], eliciting startle blink responses, EMG responses, heart rate deceleration, and skin conductance in both men and women [67]. Based on findings such as these, and with the project’s overall focus on suicide prevention, it makes sense to focus on negative arousal.

A modified version of Thomas et al.’s [68] spatial cuing task will be used. The original study measured “interpersonal body representation” via responses to exogenous visual cues that shared a known location with tactile stimulation. Specifically, this used brief flashes of light on different locations of a projected model. Using a solenoid, a tactile stimulus was then applied to the same or different body part of the participant. Participants responded verbally as quickly (RT) and accurately (error rate) as possible. The findings from Thomas et al. indicated that valid cues resulted in faster RTs and fewer errors by contrast with invalid cues, suggesting that a cue in one mode can be effective for target identification in another mode. However, this was found only in the anatomical congruence condition (i.e. my right side is your right side), not the specular (i.e. my right side is your left side), which suggests a cross-modal relationship mediated by empathy (consistent with findings on “mirror neurons”, e.g. [69]).

In the modified version of the task to be used here, the RT to cues will be treated as indicators of a previously *unknown* location of emotional feeling to which participants have responded. Participants will be requested to indicate emotional signal detection upon presentation of an emotional stimulus, which follows a visually cued location on a computer screen (a seated figure with a highlighted area of the body). Faster RTs will be more likely if there is in fact a detected bodily location that is accurately cued. Alternatively, slower RTs will be more likely if there is a detected bodily location that *could be* (cross-modally) distracted from by the presentation of a divergent visual cue.

Consideration needs to be given to possible “noise” generated by these methods. Firstly, participants have been shown to have faster responses to a visual cue presented on the same side as the responding hand, which has been interpreted as a cross-modal cueing effect (see [70]). However, this is not always considered in relation to the well-established “Simon Effect” [71], which is where RTs are faster due to a primed motor response to the target rather than an attentional cross-modal effect. For this reason, the “interpersonal body representation” paradigm appears to be an advance on other spatial cueing approaches due to the identification of anatomical versus specular differences: the “Simon Effect” appeared to have been overridden by the social nature of the cue. Plus, the cues used in the current study will always be presented centrally, with no bilateral bias.

Other possible “noise” includes:

*The effect of overt bilateral orienting*. This is essentially a cueing effect since it cuts down possible attentional foci by 50% at the point of stimulus onset. The stimulus, or key details within a stimulus, may obviously be on one side of a screen or the other. For this reason, central fixation in visual cueing tasks is necessary to prevent variation across a sample in this respect.

*Lack of luminance*. In all visual cues and stimuli, isoluminant colour changes [72], isoluminant onset cues [73], or sudden onset stimuli that do not involve a luminance change do not capture attention exogenously [74]. For this reason, standardised presentations of visual stimuli with the validated ability to capture exogenous attention should be used.

*The effect of sudden onset only*. There can be ambiguity between specifically affective salience and the more general effect of the sudden onset of any physical stimulus [75]. For this reason, blocks of trials must include neutral stimuli as well as emotional stimuli.

*Creating expectations*. In *exogenous* attention tasks, the cues may become task-relevant (i.e. predictive of a target stimulus and hence *endogenous*) [76]. In exogenous tasks, attention is *drawn to* something, whereas in endogenous trials, attention is *directed at* something with an expectation of an event (e.g. the difference between being woken in the night by a fire alarm and waiting for the school dinner bell to sound). To address this, the frequency of valid cues should, ideally, not depart from 50% of total trials (i.e. equal to chance), with suggestions in the literature (see [77]) that > 70% of overall trials may be predictive of a target (i.e. endogenous). In the emotional spatial cueing task, cues often predict the target location in 70% or more of the trials (see, for example [78]), which may facilitate task relevance.

Based on the foregoing, the spatial cueing task procedure will continue as follows:

A practice block of 16 trials will be completed (using 8 neutral emotional stimuli, involving each of the cued locations, and neutral cues).In each trial, participants fixate on a word (“Ready”) at the centre of the screen for 500 ms prior to cue onset (Fig. 2).The cue (a seated male figure) will be presented for 2000 ms in the middle of the screen, either with one of three locations highlighted at random using a red, highly luminous highlighted rectangular area (see [68, 79]), or no location highlighted. The three locations will be the chest, lower abdomen, or shins (pressed together in the image to form a single area). All highlighted areas will be the same size, colour, and luminescence. The image will be large (345 × 715 pixels), and the highlighted area as luminescent as possible within the limitations of the package used to create it (*Microsoft Office Word, version* 16.23).The emotional stimuli (selected IAPS and NAPS images; see Additional file 2) will be either 600 × 800 pixels or 800 × 600 (i.e. landscape or portrait), all at a resolution of 72 pixels/inch. The stimuli will be delivered at an inter-stimulus interval (ISI) of 200 ms, remaining for 200 ms (changes in levels of arousal do not increase significantly beyond 150 ms presentation duration [61]). With picture stimuli being presented to elicit exogenous attention, a mixture of neutral and negative emotional images will be presented to control for the effect of sudden onset of a stimulus. Further, since negative stimuli tend to reliably create the highest level of physiological arousal in men and women, this will be important for creating detectable changes in the body. Again, to ensure that the cues do not become task-relevant (i.e. predictive of a target stimulus and hence endogenous), the frequency of valid cues will be kept to below 70% of trials. Although it is not known in advance what a “valid” cue is in this bespoke variant of the spatial cueing task, for the purposes of setting up the cues these are limited to the chest and lower abdomen areas (interoceptive/visceroceptive areas), each with 31% of “valid” cues, which remains within the standard limits (i.e. 62% in total). A further 10% of trials will be “invalid”, i.e. the shins (a non-interoceptive/visceroceptive area).In 15% of trials, there will be no emotional stimulus following a cue (catch trials); plus, in a further 14% of trials, there will be a neutral cue (no cue areas highlighted)^2^.Non-catch “valid”, “invalid”, and neutral trials will be further split into calculated proportions of negative and emotionally neutral target stimuli. In total, there will be 65% negative and 20% neutral stimuli (along with the 15% catch trials).Participants are required to give a speeded response: a mouse click upon detection of a bodily change—anywhere in the body—but they will be instructed to be sure of detection (i.e. guesses are discouraged; see [77]). It is important to separate this initial response from the indication of a location in order to clearly disambiguate (i) no emotional feeling being detected and (ii) an emotional feeling being detected but when the location was not known. If no response is registered within 6000 ms, the next trial is presented.If a change was detected, then participants transition to another screen to indicate a location on a virtual body by mouse click, followed by an indication of the valence and intensity of the detected feeling (using the *Self-Assessment Manikin*; for a similar approach, see [19]). If a location was detected but it was not known where, this can be indicated by clicking outside of the body area. The time taken to give these further responses will assist with a likely longer refractory period for an embodied emotional response compared with, say, visual attendance. (See, for instance [80], where the mean cardiovascular recovery time following an emotional film stimulus—lasting up to 100 s in duration—was approximately 30 s. The estimated time per trial in the current spatial cueing task, including an inter-trial interval of 200 ms, is around 15 s, but where a picture stimulus will be presented and for a far shorter duration of 200 ms, which may then result in a shorter recovery period than a relatively lengthy film.) This process will be repeated throughout all blocks, where the cued response is exogenous.In total, there will be 6 main blocks, with a brief rest period between them, and 248 trials. Based on the percentages stated previously, this will result in 152 valid trials (76 lower abdomen; 76 chest), 26 invalid trials (shins), 37 catch trials, and 34 neutral cue trials (where no part of the body is highlighted). For each of the valid sets of trials, 58 emotional stimuli will be negative and 18 will be neutral. For invalid trials, 20 will be negative and 6 will be neutral. For neutral cue trials, 26 images will be negative and 8 will be neutral. For catch trials (no emotional stimulus), there will be 10 sets of each of the 3 bodily locations, with one set of 7 neutral locations (no areas cued on the image of a seated person).Finally, to control for order effects, blocks will be counterbalanced: one half of each of the groups (assigned at random) will complete blocks in the order 1–6. The other half will complete the blocks in reverse order.

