### Dependent variables (both tasks)

*Primary outcome*: RTs;Scores on self-report measures;Heart rate variability, heart rate deceleration.

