### Spatial cueing task

One of the interoception groups will show significantly faster reaction times (RTs) and greater response frequency to emotional stimuli regardless of cue type compared with each of the other groups after baseline; plus, there will be a greater change between baseline and follow-up. Each of the interoception groups separately and combined will show significant differences from the control group.One set of cues for the same group (i.e. the interoception group in (1)) will facilitate significantly faster RTs and greater response frequency. This set will match the target area of the body for that group (i.e. a chest cue for the cardioception group; a lower abdomen cue for the gastroception group). The “matching” cue for the other interoception group will not facilitate faster RTs or greater response frequency. If any cue facilitates faster RTs or greater response frequency for the other groups, it will be the same cue that facilitates for the interoception group in (1).This same group will display greater within-group coherence in the location of the body indicated to be active during trials compared with the other groups after baseline. It will also show the greatest change between baseline and follow-up compared with the other groups.This same group will report greater intensity compared with the other groups after baseline. It will also show the greatest change between baseline and follow-up compared with the other groups. The interoception groups combined will report greater intensity than the control group.This same group will show greater heart rate deceleration after baseline following the presentation of emotional stimuli compared with the other groups; both interoceptive groups will show greater heart rate deceleration than the control group.

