## Data analysis

Generalised Estimating Equations (GEE) will be used to analyse the two data points, including variable interactions. GEE can account for repeated measures as well as the potential problem that the primary outcome variable (RT) may not be normally distributed (although it will be continuous). Using GEE, the effects of the predictors on RT can be modelled under different circumstances, and the interrelationships between predictors can also be investigated. Significance testing will be undertaken at the *p* < 0.05 level.

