## Limitations

There are several limitations of the current design.

For the spatial cueing task, attempts have been made to make all trials comparable in terms of timings, regardless of response. However, on trials where no emotion is detected, there will be a maximum of 6 s to respond before the next trial; but on trials where there is a response, the timing may be longer if a participant takes time to consider their response, or shorter if a participant becomes fatigued and aims to rush through the trials by clicking in response to all stimuli. In order to prevent the former problem, participants will be instructed to respond as quickly as possible (to reduce the effect of cognitive appraisal). In relation to the latter problem, the use of catch trials and emotionally neutral trials will indicate this trend in a participant’s data (which can then be excluded from analysis).

Secondly, the effect of a negative stimulus in the spatial cueing task may take time to dissipate (i.e. the refractory period). Hence, there may be carry-over from one trial to the next. This limitation is addressed to a degree by having a mixture of negative and neutral stimuli, plus varied levels of standard arousal (i.e. based on previous studies of rated responses to images on the IAPS and NAPS). Plus, the time to respond in full to each stimulus before experiencing the next stimulus may approach the end of a refractory period in any case, and between blocks, there will be self-directed rest periods.

Thirdly, there is a possibility that presenting the same set of emotional stimuli over the two data points—in both main tasks—will result in habituation across the two presentations. There is, however, a low probability of this given the brief presentation of each stimulus, plus an 8-week gap between data points, and the use of the IAPS, which has been shown to resist habituation.

There is likely to be some degree of self-selection bias in the sample, given the wholly voluntary nature of the recruitment, both in terms of consenting to participate and trial completion.

Finally, as a preliminary trial, there will only be recruitment of a non-suicidal sample. This will not itself allow findings on emotion regulation to be directly related to suicidality.

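### In the spatial cueing task the RT comparison is conditional on a response that training is itself predicted to change, so it cannot be read alone as an effect on speed

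*Protocol article*

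**What the plan says.** The protocol's list of dependent variables makes RT the primary outcome for both laboratory tasks. In the spatial cueing procedure the RT comes from a click: "Participants are required to give a speeded response: a mouse click upon detection of a bodily change". The change may be felt in any part of the body, and participants are told to click only when sure of it. The time-out rule is: "If no response is registered within 6000 ms, the next trial is presented". No RT value is given to such a trial. The Limitations section describes the same window: "on trials where no emotion is detected, there will be a maximum of" 6 s before the next trial.

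Hypothesis 1 expects one interoception group to show "significantly faster reaction times (RTs) and greater response frequency to emotional stimuli regardless of cue type" after baseline, and expects each interoception group, separately and combined, to differ from control. Hypothesis 2 pairs speed and response frequency again for the matching cue. Response frequency is listed as a separate dependent variable for this task.

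The Data analysis section specifies GEE, partly because "the primary outcome variable (RT) may not be normally distributed". It does not mention trials that end without a response. The Limitations section adds that catch trials and emotionally neutral trials will reveal participants who rush by clicking at everything, "which can then be excluded from analysis".

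**The concern.** Randomisation makes the groups comparable as groups of people. It does not make the subsets of trials on which they choose to click comparable. If training lets participants notice sensations they used to miss, the trained groups' mean RT includes a class of trials that contributes nothing to the control mean. The difference in means then combines two things: any change in speed on trials that would be detected either way, and the change in which trials are counted.

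The baseline session does not remove this, because the predicted rise in responding comes after baseline. The instruction to click only when sure makes the outcome depend on a personal threshold as well, and participants learn their allocation immediately after baseline (Randomisation section).

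At stake is the interpretation of the main result of this task, on which the Sample size section bases its calculation. A null or slower RT could accompany a real gain in speed, and a faster RT could arise from a change in clicking alone.

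**Working it through.** **The plan's own figure.** The Sample size section gives partial eta-squared 0.15, alpha 0.05, 80% power and a minimum of 54 participants in three groups. Here f² = 0.15/0.85 = 0.1765, and the noncentrality at N = 54 is 54 × 0.1765 = 9.53 on 2 df. A large-sample chi-square test gives power 0.795 at 54 and reaches 80% at 55, so the figure reproduces closely. The exact F version needs 58, which the target of 70 covers. The planned effect is thus an RT effect, with no allowance for a change in which trials yield an RT.

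**Illustration of the selection effect.** All inputs are assumptions, because the protocol gives no detection rates. Before training, a share p0 = 0.40 of trials is detected, with mean RT 1900 ms. Training speeds those trials by g = 190 ms, to 1710 ms, and raises detection to p1 = 0.60. If control stays at 40% and 1900 ms, the changes below are also the between-group differences in change.

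- Observed mean RT = (0.4 × 1710 + 0.2 × m)/0.6, where m is the mean RT of newly detected trials.
- Restricted mean time over all trials = 0.4 × 1710 + 0.2 × m + 0.4 × 6000. Before training it is 0.4 × 1900 + 0.6 × 6000 = 4360 ms.

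| New detections relative to 1710 ms | Observed mean RT | Change from 1900 | Restricted mean | Change from 4360 |
|---|---|---|---|---|
| 500 ms faster | 1543 | −357 | 3326 | −1034 |
| equal | 1710 | −190 | 3426 | −934 |
| 500 ms slower | 1877 | −23 | 3526 | −834 |
| 570 ms slower | 1900 | 0 | 3540 | −820 |
| 1000 ms slower | 2043 | +143 | 3626 | −734 |

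The true gain on already-detected trials is 190 ms in every row.

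**Break-even.** The observed difference is zero when new detections average g × p0/(p1 − p0) above the control mean. Here that is 190 × 0.4/0.2 = 380 ms above 1900 ms, which is the 570 ms row. For a 100 ms gain it is 400 ms (detection 40% to 50%), 200 ms (40% to 60%), 133 ms (40% to 70%) or 300 ms (60% to 80%).

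**Simulation.** Each trial was given a latent signal strength and counted as detected above a threshold. Mean RT was 2000 ms with noise SD 400 ms, the true gain was 100 ms, and there were 1,000,000 trials per arm. RT was made slower by 0, 150, 300 or 450 ms for each SD of weaker signal. Observed differences, treated minus control:

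- detection 40% to 60%: −99, −51, −5, +45 ms;
- detection 40% to 70%: −100, −31, +40, +110 ms;
- detection unchanged at 40%: −97 to −102 ms.

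There is no distortion if detection does not differ between groups, or if RT does not depend on signal strength.

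**Power.** If selection left 75% or 50% of the planned RT effect, the noncentrality would be multiplied by 0.75² or 0.5², and power at N = 54 would fall from about 0.80 to 0.53 or 0.26.

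**What an all-trials measure would pick up.** In the 500 ms slower row, faster responding on already-detected trials contributes 0.4 × 190 = 76 ms of 834 ms (9%). In the 1000 ms slower row it contributes 76 of 734 ms (10%). The rest is detection. With no speed gain at all, looser clicking alone (40% to 60%, extra clicks at 2400 ms) gives 760 + 480 + 2400 = 3640 ms, an apparent improvement of 720 ms.

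**The case against.** RT on responded trials is a legitimate construct here: the task treats RT as a sign of a location to which the participant has responded. Response frequency is measured and hypothesised separately, so a detection gain would be visible. Felt intensity is rated on responded trials and the same stimuli are used at both visits, so one could check whether extra detections are weaker or slower. All of this stands, and it is why RT should be kept. It does not make the RT contrast interpretable alone, since seeing that frequency differs does not show how much of the RT difference comes from it.

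Nothing in the document shows that newly noticed sensations are slower. That is correct: the direction and size of any bias are unknown. A reader might infer that the analysis will hide or reverse a real gain, but fast extra clicks would exaggerate it instead.

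A reader might also infer that the GEE discards timed-out trials. That is the natural reading of the procedure, but the Data analysis section does not say so, and such coding is commonly left to a fuller plan. The point does not rest on that omission. It rests on pairing an RT that needs a click with a hypothesis that training changes clicking.

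Finally, a reader might take the exclusion passage to mean that people whom training improved will be removed. The Limitations section is aimed at fatigued clicking at all stimuli, and catch trials contain no stimulus, so clicking on them is not the gain hypothesis 1 predicts. What remains is narrower: emotionally neutral trials do contain a stimulus, and using them as a flag could catch genuine responders.

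**Conclusion.** The point holds for the spatial cueing RT. Its between-group contrast is conditioned on a post-randomisation response that the protocol's own first hypothesis expects to differ. Under the assumed rates, a 190 ms gain could appear as anything from −357 to +143 ms. These figures show what is possible and estimate nothing about this trial.

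Two wider readings are not supported. The primary outcome as a whole is not compromised: the stop/signal RT comes from key presses to symbols and does not depend on reporting a bodily change. Nor does the finding require RT to be replaced. A censored all-trials measure is about 90% detection in the two slower-detection examples, and a looser click criterion alone could move it. The two measures fail in different ways, which is the reason to report both.

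**What to change.** For the spatial cueing task:

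- Keep RT on responded trials, state that it is conditional on response, and say that it will not be read alone as a training effect on speed.
- Pre-specify beside it a baseline-adjusted analysis of time to detection on all target trials, censored at 6000 ms: either a restricted mean with non-response set to 6000 ms, or a Cox model with participant-clustered errors.
- Analyse response frequency against catch-trial false alarms, by d-prime or a stimulus-presence-by-group term, so that looser clicking is not read as better detection. The design already has 37 catch trials.
- Base any exclusion for indiscriminate clicking on catch-trial responses, with a threshold fixed in advance and applied blind to group, and report results with and without those participants.

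The cost is analysis wording and additional reporting; the task already records a click time or a time-out on each target trial. The drawback is that censored time mixes speed with detection and is sensitive to response criterion, so RT, frequency and false alarms must be shown together with it. Because RT stays in place, the sample size basis is unchanged.

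### Catch trials are split equally over the three body locations while picture trials are not, so the cue carries information about whether a picture follows, and contrasts of chest or abdomen with shins could reflect expectancy

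*Protocol article*

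**What the plan says.** All the counts stand in the numbered procedure of the protocol article's section on the spatial cueing task. The trial totals are "152 valid trials (76 lower abdomen; 76 chest), 26 invalid trials (shins), 37 catch trials, and 34 neutral cue trials". The picture trials of each cue type are then split by picture content:

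- Chest and abdomen: "For each of the valid sets of trials, 58 emotional stimuli will be negative and 18 will be neutral".
- Shins: "For invalid trials, 20 will be negative and 6 will be neutral".
- No area highlighted: "For neutral cue trials, 26 images will be negative and 8 will be neutral".

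Catch trials, in which a cue is shown but no picture follows, are introduced as "In 15% of trials, there will be no emotional stimulus following a cue (catch trials". Their split by cue is "there will be 10 sets of each of the 3 bodily locations, with one set of 7 neutral locations".

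The same procedure sets a design aim: "to ensure that the cues do not become task-relevant (i.e. predictive of a target stimulus and hence endogenous". The means given is to hold chest and abdomen cues together below 70% of trials; the planned share is 62%. The discussion of noise before the procedure lists the creation of expectations among the problems to be controlled.

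Cue position (shins, chest, lower abdomen, or any area versus none) is a listed predictor for this task. The task description reads faster responses after a cue as a sign that the cue matched a bodily location that was really felt.

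**The concern.** An equal number of catch trials per location looks even-handed, but shins are cued far less often than chest or abdomen. Ten catch trials are a small share of the chest trials and a large share of the shin trials. A participant who picks this up would expect a picture more often after a chest or abdomen cue than after a shin cue. The cue stays on screen for 2000 ms and a 200 ms gap follows, so there is time for expectancy to act.

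Shins are the only highlighted location outside the viscera. If responses are faster or more frequent after chest or abdomen cues than after shin cues, the plan would take this as support for localised feeling (RQ1). Learned readiness could produce the same pattern, and the within-person comparison could not tell the two apart. The Limitations section deals with fatigue clicking, carry-over and habituation, but not with this.

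**Working it through.** **Inputs** (all from the spatial cueing procedure): picture trials 76, 76, 26, 34; catch trials 10, 10, 10, 7; stated totals 37 catch and 248 overall.

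**Reproducing the plan's figures.** Catch trials: 3 × 10 + 7 = 37, and 0.15 × 248 = 37.2, so 37 agrees. Negative pictures: 58 + 58 + 20 + 26 = 162, and 162/248 = 65.3% (stated 65%). Neutral pictures: 18 + 18 + 6 + 8 = 50, and 50/248 = 20.2% (stated 20%). The overall total is 76 + 76 + 26 + 34 + 37 = 249 against the stated 248, a one-trial slip; the stated percentages give 31 + 31 + 10 + 15 + 14 = 101.

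**Are catch trials extra to the cue counts?** Yes: 58 + 18 = 76, 20 + 6 = 26 and 26 + 8 = 34, so every trial in those counts carries a picture.

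**Chance of no picture given the cue** = catch / (catch + picture trials):

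| Cue | Picture | Catch | All | No picture | Picture follows | Negative picture follows |
|---|---|---|---|---|---|---|
| Chest | 76 | 10 | 86 | 11.6% | 88.4% | 58/86 = 67.4% |
| Lower abdomen | 76 | 10 | 86 | 11.6% | 88.4% | 58/86 = 67.4% |
| Shins | 26 | 10 | 36 | 27.8% | 72.2% | 20/36 = 55.6% |
| No highlight | 34 | 7 | 41 | 17.1% | 82.9% | 26/41 = 63.4% |

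Ratio of no-picture rates: shins to chest or abdomen, 27.8/11.6 = 2.39; no highlight to chest or abdomen, 17.1/11.6 = 1.47.

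**Sensitivity to the reading.** If the 76 and 26 were taken to include the catch trials, which the picture splits contradict, the ratio would be (10/26)/(10/76) = 2.92. The imbalance holds either way.

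**Does the 70% rule help?** Chest and abdomen cues make up 152/248 = 61.3% of trials, or (86 + 86)/249 = 69.1% with their catch trials counted. The rule is met both ways while the table above stands. It limits how often a cue is shown, not what follows it.

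**Which contrasts are exposed?**

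- Chest or abdomen versus shins: 11.6% v 27.8%, exposed.
- Chest or abdomen versus no highlight: 11.6% v 17.1%, weakly exposed.
- Any area versus none: 30/208 = 14.4% v 17.1%, close to balance.
- Chest versus abdomen: 11.6% each, with the same 58/18 picture split, balanced.
- Between groups, or baseline versus follow-up: one schedule for all, so largely protected.

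**The case against.** The strongest objection concerns reach. A reader might infer that the schedule biases the test of hypothesis 2, or the localisation test as a whole, in the hoped-for direction. The document does not support that. Hypothesis 2 predicts that one trunk cue helps one trained group and that the other trained group's matching cue does not help. Its key contrast is chest versus abdomen by group, and there the catch rates and picture splits are identical. Expectancy that raises both trunk cues equally cannot create the predicted asymmetry. Measured against shins, it would make the second cue seem to help too, which works against the hypothesis. Comparisons between groups and over time share one schedule and would be affected only if training changed sensitivity to the contingency. All of this stands, and it limits the point.

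A reader might also take it as fact that people respond more readily after trunk cues. The document has no evidence on this. There are 36 shin-cued trials in six blocks, 36/6 = 6 per block if spread evenly, with 10/6 = 1.7 of them catch trials. Participants click on a felt bodily change, not on picture onset; they must be sure of it and have 6000 ms. Learning may be weak. This stands too: the confound is possible, not shown.

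Equal catch counts could be defended as giving the same number of false-alarm trials per location. That is a real benefit, since response frequency is an outcome and catch status a predictor. But the protocol does not state it as a purpose. The use it does state, spotting participants who click at everything, works with catch trials pooled over cues.

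Finally, the sentence that introduces catch and neutral-cue trials carries a footnote whose text is not in the document at hand. It might bear on the point.

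**Conclusion.** The point holds in a limited form. On the protocol's own counts, the no-picture rate is 2.4 times as high after shins as after chest or abdomen (27.8% v 11.6%), with no highlight in between (17.1%). The cue therefore predicts the target, against the stated aim, and the only stated safeguard does not address it. This part is arithmetic and needs no assumption.

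The consequence for the results is conditional. If participants learn the contingency, within-person differences between chest or abdomen and shins, and less so no highlight, could be expectancy. No bias in milliseconds can be derived from the document. Chest versus abdomen and the group and time contrasts are not materially exposed, so the main hypotheses are not undermined. The 249 against 248 is a trivial slip and adds nothing to the argument. The change is worth making because it serves the protocol's own rule at almost no cost.

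**What to change.** Allocate catch trials in proportion to cue frequency. The exact shares of 37 are 37 × 76/212 = 13.3 each for chest and abdomen, 37 × 26/212 = 4.5 for shins and 37 × 34/212 = 5.9 for no highlight. Two roundings serve:

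- 13/13/5/6 keeps the stated 37. No-picture rates are 13/89 = 14.6%, 14.6%, 5/31 = 16.1% and 6/40 = 15.0%, and the shins-to-chest ratio falls to 1.10. The stated overall total should then read 249.
- 13/13/4/6 gives 36 catch trials and 212 + 36 = 248, the stated total, with shins at 4/30 = 13.3%. The catch count should then read 36.

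All picture trials stay as they are; only the trial list and the stated totals change. The cost is a less precise shin-specific false-alarm rate for each participant, from 4 or 5 trials instead of 10. Pooled catch trials still detect indiscriminate clicking.

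If the schedule is kept, or sessions have already been run (the article gives August 2019 as completion), report the no-picture rates by cue. Do not read chest- or abdomen-versus-shins differences as evidence of localisation. Rest that inference on chest versus abdomen and on the group-by-time-by-cue contrasts.
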